## Abstract

**Background:**

Volar plate injuries are a common hand injury and complications associated with this injury such as a fixed flexion deformity, persistent pain and oedema can have a significant impact on a person’s function. The literature reports these injuries are treated using various splinting materials such as thermoplastic, in varying degrees of proximal interphalangeal joint flexion or buddy loops. Despite volar plate injuries being reported as common, optimal non-surgical treatment of these injuries remains unclear.

This study aims to investigate whether a dorsal blocking orthosis in a neutral position (0^0^) is more effective than buddy loops for a volar plate injury to the proximal interphalangeal joint in preventing a fixed flexion deformity, reducing pain, managing oedema, and promoting function.

**Methods:**

This study is a single-centre, prospective parallel-group, single blinded (assessor), randomised clinical trial. Patients between 18–65 years, who have sustained a volar plate injury to a single digit, have adequate cognitive functioning and give written informed consent will be invited to participate in this study. Patients will be randomised to either the control group where they will be fitted with buddy loops and commence early active motion exercises or the experimental group where they will receive a dorsal thermoplastic orthosis in a neutral position and commence early active motion exercises. The primary outcome measure is passive proximal interphalangeal joint extension and secondary outcome measures include passive range of motion, total passive motion, active range of motion, total active motion, grip strength, oedema, pain, function and adherence to treatment. Assessments will be completed until 8 weeks following commencement of treatment. The sample size calculation indicates that 23 patients is required in each group. With an expected dropout rate of 25% a total of 32 patients will be enrolled in each group.

**Discussion:**

This study will assist in trying to improve treatment of volar plate injuries and assist in reducing complications associated with volar plate injuries, potentially reducing the need for prolonged hand therapy.

**Trial registration:**

This trial has been registered with the Australian New Zealand Clinical Trials Registry (ACTRN12622001425785p). Ethical approval has been granted by the South Eastern Sydney Local Health District ethical committee (2022/ETH01697).

**Supplementary Information:**

The online version contains supplementary material available at 10.1186/s12891-023-06192-5.

## Background

Volar plate injuries are a common injury [1] and are often sustained during sport, whereby the finger is pushed back, stretching the volar plate [2]. This hyper-extension force can often cause an avulsion of the volar aspect of the middle phalanx where the volar plate inserts or can cause a dorsal dislocation of the Proximal Interphalangeal Joint (PIPJ) [3].

Volar plate injuries are reported to be a common injury in the hand [4]. The Eaton classification is used in the literature to describe the severity of volar plate injuries to the PIPJ. Eaton type I injuries are described as a hyperextension injury whereby there is either a partial or complete avulsion of the volar plate from the middle phalanx and may or may not include a bone fragment; Eaton type II are described as a dorsal dislocation with a complete avulsion of the volar plate and a bilateral split in the collateral ligament; Eaton type III are described as a fracture dislocation where the volar plate is avulsed from its insertion and creates a disruption at the base of the middle phalanx on the volar surface. These injury types are subdivided into stable (IIIa) or unstable (IIIb) [5].

Although volar plate injuries are common, the optimal way to conservatively treat them is still not clear [5]. Historically, volar plate injuries have been treated by splinting the joint in varying degrees of PIPJ flexion (10^o^ – 30°) [6, 7] using Plaster of Paris, an aluminium or plastic orthosis [7–10]. Protected mobilisation has also been demonstrated using a dorsal thermoplastic orthosis that blocks the PIPJ from completely extending but allows the patient to flex the injured digit by undoing the Velcro straps [11]. Although early protected motion has been shown to be safe and assists in preventing stiffness into flexion, the risk of a Fixed Flexion Deformity (FFD) remains due to the soft tissues around the joint healing in a shortened position due to the positioning of the joint in a flexed position [12].

An alternative in the literature, that also allows protected mobilisation, is buddy loops [6]. Buddy loops involve ‘buddying’ the injured digit to a border digit using a strap or tape. It provides support and protection while allowing early motion. Research suggests that buddy loops can be effective in producing good Range of Motion (ROM) outcomes for volar plate injuries [13], but the evidence reported is largely retrospective or they have a large proportion of children and adolescents included in the cohort.

Another alternative treatment is to immobilise the joint in a neutral position using a dorsal thermoplastic orthosis. A recent study by Stanley, Seifman [7] compared treatment of volar plate injuries by splinting the PIPJ in 30° of flexion and compared it to splinting the joint in neutral (0°). The study concluded that splinting the joint in a neutral position led to better extension of the PIPJ and did not lead to issues with instability or hyper extensibility. However, the research is retrospective, and the groups were uneven with 105 participants in the group with the PIPJ in flexion and only 20 were the PIPJ was positioned in neutral, reducing the statistical power of the study.

Positioning the PIPJ in a neutral position has also been demonstrated in cadaveric studies. A study completed by Tyser, Tsai [14] found that volar plate injuries with up to a 20% bony defect remained stable in a neutral position during testing, whereas a bony defect of up to 40% was reported to be variable and the threshold for PIPJ stability. This has been reinforced by Caravaggi, Shamian [15] who found that collateral ligament and volar plate injuries alone as well as fractures of less than 30% of the joint surface were unlikely to be unstable.

Looking at the reported treatment interventions, the research suggests that while splinting the PIPJ in a flexed position does provide joint stability, it may also be a significant contributor to the most reported complication of a FFD [16].

Buddy loops are noted as a cost effective and efficient method for treatment of volar plate injuries [6]. They promote early active motion however, it is unclear if they provide adequate positioning to prevent a FFD, particularly in the presence of oedema, pain or in Eaton IIIa classified injuries.

Based on the research available, splinting the PIPJ in a neutral position may result in superior outcomes as it positions the joint in an optimal resting position and allows protected early active motion. Using buddy loops to treat volar plate injuries has been reported to provide good Active Range of Motion (AROM) outcomes due to the early and easy commencement of early active motion, however, could still lead to the development of a FFD due to the natural resting posture of the digit. Due to the limitations in the current literature, further research is required to determine the optimal way to treat these injuries.

The aim of this study is to investigate whether a dorsal blocking orthosis (splint) in a neutral position (0°) is more effective than buddy loops in the treatment of a volar plate injury. Specific hypotheses will address; splinting the PIPJ in a neutral position produces a) a lower average extension contracture of a FFD than splinting in buddy loops; b) lower mean pain scores than buddy loops; c) lower mean oedema measure than buddy loops; and d) splinting the PIPJ in a neutral position results in changed adherence to treatment compared to buddy loops.

## Methods

The study is a randomised controlled, single-centre, parallel, single blinded (assessor) trial.

### Participants

All patients who attend the Sydney Hospital Hand Clinic between March 2023 - September 2024 and meet the selection criteria will be invited to participate in the study.

Patients will be invited to participate in this study if they are aged 18–65 years, are diagnosed with a closed volar plate injury to a single digit (Eaton classification I, II, IIIa), do not require surgical intervention, have adequate cognitive functioning, in that they are able to understand written and verbal information regarding their injury and participation in the study, have their first treatment at Sydney Hospital within 14 days of sustaining their injury and can give written informed consent.

Patients will be excluded from the study if they have a concomitant tendon or nerve injury, other fracture, vascular injury, or open injury, a previous or existing condition that affects the same or contralateral digit resulting reduced AROM and/or pain.

### Sample size

A mean difference of 10° in passive PIPJ extension scores between the control and experimental groups is deemed to be clinically relevant. Based on a quality improvement project on volar plate injuries at Sydney Hospital, a standard deviation of 10° in passive PIPJ extension scores is estimated [17]. To be able to detect this difference with 90% power at the 5% significance level, 23 participants will be required in each group. Factoring in a dropout rate of 25% brings the total to 32 participants in each group.

At Sydney Hospital Hand Clinic, there were 149 presentations for volar plate injuries in the period between 22/06/2017 – 18/12/2018. It is anticipated that there will be a 50% uptake of patients consenting to be involved in the study. Therefore, recruitment and data collection is anticipated to take 18 months.

### Randomisation

Enrolment and randomisation will be conducted after obtaining signed informed consent from a patient.

To ensure sufficient and balanced treatment groups, there will be 64 random draws of ‘orthosis’ or ‘buddy loops’ in blocks of four. That is, there will be two thermoplastic orthoses and two buddy loops in each block of four. Each of the 64 random draws will be printed on a card. Each card will be placed in a separate sealed opaque envelope. The envelopes will be numbered on the outside in draw order. Therapists will be instructed on the importance of drawing the envelopes in correct sequence and adhering to the treatment written on the card. The chief investigator or one of the assigned treating hand therapists will take the next envelope in the sequence.

If participants consent, they will be randomised to either the experimental or the control group. The participant flow is shown in Fig. 1. Each eligible patient presenting to the hand clinic will be invited to participate in the study.

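### Fixed blocks of four, drawn by staff who are not blinded at a single clinic, let a well-informed drawer deduce up to a third of allocations

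*Protocol article*

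**What the plan says.** All of the following is in the protocol article.

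- **List.** Under Randomisation, "there will be 64 random draws of ‘orthosis’ or ‘buddy loops’ in blocks of four", and "there will be two thermoplastic orthoses and two buddy loops in each block of four". No other block size and no stratification factor is mentioned, so the list is 16 consecutive blocks of four.
- **Concealment.** "Each of the 64 random draws will be printed on a card", and "Each card will be placed in a separate sealed opaque envelope". The envelopes carry their draw order on the outside, and therapists are told to take them in sequence.
- **Who draws.** "The chief investigator or one of the assigned treating hand therapists will take the next envelope in the sequence".
- **When.** "Enrolment and randomisation will be conducted after obtaining signed informed consent from a patient". The same section says that every eligible patient who presents will be invited.
- **Blinding.** Methods: "The study is a randomised controlled, single-centre, parallel, single blinded (assessor) trial". The Blinding section keeps assessors separate from the treating therapist. It does not blind the treating therapists, and it could not, because they manage patients in a visible device.
- **Entry.** Participants must not need surgery, must have no earlier condition of the digit that limits motion or causes pain, and must "have adequate cognitive functioning, in that they are able to understand written and verbal information regarding their injury and participation in the study".

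**The concern.** A sealed envelope stops staff from reading the next card. It does not stop them from working out what the card must say. With a known block of four and a number on each envelope, the position in the block is visible. Once two identical devices have been given in a block, the rest of that block is settled, and the fourth envelope is always settled.

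Prediction matters before consent: in whom to approach, when, and how the criteria that need judgement are applied. The Background gives staff a possible reason to prefer one device for some patients. It questions whether buddy loops position the joint well enough when there is oedema, pain or an Eaton IIIa injury, and the stated hypotheses on deformity, pain and oedema favour the orthosis. The list is not stratified by Eaton type. The Sample size section expects only half of patients to consent, so selective non-entry would not stand out.

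Analysis is a weak remedy. Data analysis offers ANCOVA for baseline differences, but Table 1 schedules passive PIPJ extension only at weeks 3, 5 and 8. The primary outcome therefore has no baseline value to adjust for, and unmeasured selection cannot be adjusted away in any case.

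**Working it through.** **The plan's own figures.** The article gives no predictability figure. Its total is consistent with the block design: 2 × 32 = 64 = 16 × 4. The sample size also reproduces. For a difference of 10° and an SD of 10°, 90% power and two-sided 5% (sidedness assumed), the t-test solution is 22.02, rounded up to 23 per group. Then 23 / 0.75 = 30.7, against the stated 32, which fits rounding up to whole blocks. The present point does not affect the sample size.

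**Inputs.** Block size 4, split 2:2, 64 allocations, no strata (Randomisation).

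**Certain allocations when all earlier ones in the block are known.** There are 6 equally likely orderings.
- Positions 1 and 2: never certain.
- Position 3: certain if the first two match, which is 2 of 6 orderings = 1/3.
- Position 4: always certain.
- Expected per block: 1 + 1/3 = 4/3. Share: (4/3)/4 = 33.3%. Over 16 blocks: 16 × 4/3 = 21.3 of 64.
- The count is 16 + Binomial(16, 1/3), with a 95% range of about 18 to 25.

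**Best guess for the same observer.** The chances of being right at positions 1 to 4 are 1/2, 2/3, 2/3 and 1. Their sum is 17/6, and (17/6)/4 = 17/24 = 70.8%, or 45.3 of 64. With no information it is 50%.

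**Partial sight.** Suppose each earlier allocation is known independently with probability p.
- Position 3 is certain if the first two match and both are known: p²/3.
- Position 4 is certain if the two matching allocations among the first three are both known: p².
- Share: (p²/3 + p²)/4 = p²/3.

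| p | Certain share | Of 64 |
|---|---|---|
| 1 | 33.3% | 21.3 |
| 0.9 | 27.0% | 17.3 |
| 0.75 | 18.8% | 12.0 |
| 0.5 | 8.3% | 5.3 |

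**Randomly varying blocks.** These are simulated for an observer who sees every past allocation and knows which sizes are possible, but not their order.

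| Design | Certain, of 64 | Best guess right |
|---|---|---|
| Fixed 4 | 21.3 (33.3%) | 70.8% |
| 4, 6 or 8 at random, total not used by the observer | about 1.4 (2.2%) | about 68% |
| 4, 6 or 8 summing to 64, total known to the observer | about 2.9 (4.6%) | about 68% |

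Varying the sizes removes nearly all the certainty but little of the advantage in guessing.

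**The case against.** A fair defence has four parts.

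1. **One third is a ceiling.** It needs a person who knows the block size and has seen every earlier allocation in the block. Several people share the drawing, and the article does not say that each sees the others' allocations. This stands, and it is why the figure is given as a range in p. The upper end is still plausible at one clinic, above all for the chief investigator.
2. **There are real safeguards.** Envelopes are sealed, opaque and numbered, consent comes first, and every eligible patient is to be invited. First treatment must fall within 14 days of injury, which limits deferral. The cognition criterion is defined, so it leaves less room for judgement than its label suggests. These narrow the opportunity to act on a prediction, but they do not prevent the prediction.
3. **Recruiter and drawer may be different people.** The article says who takes the envelope. It does not say who invites patients or judges eligibility, or that the chief investigator fits devices. The overlap is an assumption.
4. **Some details belong in the full protocol.** Who prepares the list, and what is logged on an envelope before opening, are points a condensed article may leave out. Silence on them is not part of this point. The block size and the drawers are stated, so they can be judged.

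A reader might infer that a third of allocations will in fact be known in advance, or that concealment has failed. The article supports neither. It shows that prediction is possible, not that anyone will predict, act on it or bias the result.

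**Conclusion.** The point holds as a weakness in a stated design choice. A fixed block of four, published in the article and used by drawers who are not blinded at one site, lets up to 33% of allocations (about 21 of 64) be deduced with certainty. The share is about 19% if each earlier allocation is known with probability 0.75, and 8% if 0.5.

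The ceiling assumes full sight of earlier allocations in the block and knowledge of its size. The step from prediction to selection bias further assumes that the person who can predict also influences entry, which the article does not say. The size of any resulting bias in the treatment effect cannot be derived from the article. The change should be made because it is cheap and closes most of the route to certain knowledge, not because bias has been shown.

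**What to change.** **If envelopes remain unopened.** Generate the list, or the part not yet opened, with randomly varying block sizes such as 4, 6 and 8 that sum to the planned total. If recruitment has begun, start the new part at the end of a completed block of four. The number remaining is then a multiple of four and can be filled exactly. Withhold the sizes from clinic staff and from public documents until recruitment ends.

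**Cost.** A new list and reprinted cards. A block of eight can put the arms out of balance by up to 4 partway through, against 2 for a block of four. There is no imbalance at the end if the blocks sum to the total.

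**Limit.** Certain allocations fall to roughly 1 to 3 of 64, but an observer who sees all past allocations still guesses right about 68% of the time. The rule to invite every eligible patient therefore still matters.

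**If recruitment is complete.** Report the predictability as a limitation. From the envelope order, mark which allocations were deducible, and compare baseline features of deducible and non-deducible allocations, by arm. Active motion, pain, PRWHE and oedema are available from the initial assessment in Table 1; passive PIPJ extension is not. With about 21 against 43 allocations, a null comparison would be weak reassurance.

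### Eaton type is known for every patient at entry but is neither a stratification factor nor a pre-named covariate; fixing it in the primary model is a cheap, modest gain in precision

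*Protocol article*

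**What the plan says.** **Allocation.** Under Randomisation, "there will be 64 random draws of ‘orthosis’ or ‘buddy loops’ in blocks of four", and "there will be two thermoplastic orthoses and two buddy loops in each block of four". There is one numbered series: "The chief investigator or one of the assigned treating hand therapists will take the next envelope in the sequence". No stratification factor is named, and a single series drawn in strict order leaves no room for one.

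**Eaton type.** Under Participants, a patient must be "diagnosed with a closed volar plate injury to a single digit (Eaton classification I, II, IIIa". The Background states that "The Eaton classification is used in the literature to describe the severity of volar plate injuries to the PIPJ". It also says it is unclear whether buddy loops position the digit well enough to prevent a fixed flexion deformity, "particularly in the presence of oedema, pain or in Eaton IIIa classified injuries".

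**Analysis.** Data analysis lists independent-samples t-tests on follow-up means, ANCOVA for baseline differences between the groups, and repeated-measures ANOVA or linear mixed models, all by intention to treat. No covariate is named.

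**Baseline.** Table 1 ticks the primary outcome at weeks 3, 5 and 8 only. Active PIPJ motion, pain and oedema are ticked at the initial visit.

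**The concern.** The trial pools injuries running from hyperextension (type I) through dorsal dislocation (II) to stable fracture dislocation (IIIa). Blocks of four equalise the number of patients per arm but do almost nothing to equalise the mix of types. With 32 per arm, a visible excess of the more severe injuries in one arm is quite possible, and a reader could then not easily tell device from severity.

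Two features of the analysis leave this open. The t-test makes no use of Eaton type, so any effect of type on extension counts as noise. The ANCOVA is tied to differences seen in the data, so the covariates would be chosen after looking. A baseline value of the outcome, which would often absorb severity, is not scheduled for passive PIPJ extension.

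**Working it through.** **Inputs from the Sample size section.** The target is "A mean difference of 10° in passive PIPJ extension scores between the control and experimental groups is deemed to be clinically relevant". For the spread, "a standard deviation of 10° in passive PIPJ extension scores is estimated". Power is 90%, the significance level 5% (taken as two-sided), and dropout 25%.

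**Step 1: the plan's own figure.**
- Normal approximation: 2 × (1.960 + 1.282)² × (10/10)² = 21.01, so 22 per group.
- Two-sample t-test (noncentral t): 22.02, so 23 per group, as stated. Power at 23 is 91.2%.
- Dropout: 23/0.75 = 30.7, so 31. The plan's 32 is one patient more cautious. The sample size reproduces.

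**Step 2: how often the arms differ in severity.** The documents give no Eaton mix, so a range is assumed. If m of 64 patients are type II or IIIa, the number falling in one arm of 32 is roughly hypergeometric(64, m, 32). The chance that the arms differ by 6 or more such patients (6/32 = 19 percentage points) is:

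| m of 64 | Chance |
|---|---|
| 10 | 8.2% |
| 16 | 14.8% |
| 32 | 21.1% |

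Simulating the actual blocks-of-four scheme gives 7.9%, 14.9% and 20.8%, so blocking gives almost no protection here.

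For type IIIa alone, at an assumed 10, 20, 30 or 50% of patients, the chance of a gap of at least 15 points is 6, 16, 22 or 26%.

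**Step 3: how far that moves the result.** The effect of type on passive extension is not given either, so gaps of 5° and 10° are assumed. The SD of the resulting shift in the arm difference is:
- 5° gap: 0.4–0.6°.
- 10° gap: 0.7–1.3°.

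For comparison, the standard error of the arm difference is 10 × √(2/32) = 2.5° at 32 per arm and 10 × √(2/23) = 2.9° at 23. The target is 10°.

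**Step 4: what modelling Eaton type gains.** With a share p in the more severe stratum and a gap d, type explains p(1 − p)d²/10² of the planned variance. At p = 0.25:

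| Gap d | Variance share | SE factor √(1 − share) | Residual SD | Power at 23 per group |
|---|---|---|---|---|
| 0° | 0 | 1.000 | 10.0° | 91% |
| 5° | 0.25 × 0.75 × 25/100 = 0.047 | 0.976 | 9.76° | 92% |
| 10° | 0.25 × 0.75 × 100/100 = 0.1875 | 0.901 | 9.01° | 96% |

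In sample-size terms, 1/(1 − share) is 1.05 and 1.23 for the two gaps. The one degree of freedom spent on the covariate is ignored.

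**Step 5: what stratified envelopes add.** Blocks of four within each of two strata cap the difference in a stratum at 2 patients, or 2/32 = 6 points. That improves balance. It does not shrink the error term of an unadjusted t-test, so the gain in Step 4 comes from the model term.

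**The case against.** Unstratified blocked randomisation is a sound design. Chance imbalance does not bias the estimate on average, and the 5% level and stated power already allow for it. This stands in full.

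The planned ANCOVA could take up an Eaton imbalance, and naming covariates is often left to an analysis plan that is not shown here. This stands in part. What the article does state is that adjustment answers to observed differences, and that is the weaker rule. Baseline active PIPJ motion, pain and oedema are collected and might carry some of the severity, but none is named as a covariate.

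A reader might infer that the plan names IIIa as the case where buddy loops fail. It does not. It lists IIIa beside oedema and pain and says only that the matter is unclear. The remark also concerns how one device performs in IIIa; it is not a statement that IIIa joints extend less under either treatment. The prognostic effect used in the working is therefore an assumption, and a covariate main effect would not answer whether the device effect differs by type.

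The size is also modest. The 10° gap is as large as the whole treatment target, and at 5° the gain is about 2%.

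**Conclusion.** The point holds as a cheap improvement to the plan. Neither the allocation scheme nor the sample size is wrong, and 23 evaluable and 32 enrolled per group need not change.

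What remains is that a severity grade known for every patient at entry is not used in a fixed way in either allocation or analysis, and that the stated rule for adjustment depends on the data. The gain is conditional on two assumed figures: 25% of patients in the more severe stratum, and a gap of 5° to 10° between strata. If type has little effect on passive extension, the precision gain is close to nil and the benefit is mainly that the adjustment is settled in advance.

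**What to change.** 1. Record Eaton type on the enrolment form before the envelope is drawn.
2. Name Eaton type as a fixed covariate in the primary analysis of passive PIPJ extension, to be included whatever balance is observed, and replace the imbalance-triggered wording for the ANCOVA. If the envelopes are already in use, this step alone, settled before any unblinded analysis, captures the precision gain.
3. If the envelopes are not yet in use, also prepare two numbered series by Eaton type, each 1:1 in blocks of four. Fix the split in advance. I–II versus IIIa matches the type that the Background singles out; pooling II with IIIa would leave IIIa free to be unbalanced within its stratum.

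**Cost.** One degree of freedom, some spare cards, and a possible imbalance of up to two patients per stratum from an unfinished block.
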